## Abstract

**Background:**

Health service change is difficult to achieve. One strategy to facilitate such change is the clinical pathway, a guide for clinicians containing a defined set of evidence-based interventions for a specific condition. However, optimal strategies for implementing clinical pathways are not well understood. Building on a strong evidence-base, the Psycho-Oncology Co-operative Research Group (PoCoG) in Australia developed an evidence and consensus-based clinical pathway for screening, assessing and managing cancer-related anxiety and depression (ADAPT CP) and web-based resources to support it - staff training, patient education, cognitive-behavioural therapy and a management system (ADAPT Portal). The ADAPT Portal manages patient screening and prompts staff to follow the recommendations of the ADAPT CP. This study compares the clinical and cost effectiveness of two implementation strategies (varying in resource intensiveness), designed to encourage adherence to the ADAPT CP over a 12-month period.

**Methods:**

This cluster randomised controlled trial will recruit 12 cancer service sites, stratified by size (large versus small), and randomised at site level to a standard (Core) versus supported (Enhanced) implementation strategy. After a 3-month period of site engagement, staff training and site tailoring of the ADAPT CP and Portal, each site will “Go-live”, implementing the ADAPT CP for 12 months. During the implementation phase, all eligible patients will be introduced to the ADAPT CP as routine care. Patient participants will be registered on the ADAPT Portal to complete screening for anxiety and depression. Staff will be responsible for responding to prompts to follow the ADAPT CP. The primary outcome will be adherence to the ADAPT CP. Secondary outcomes include staff attitudes to and experiences of following the ADAPT CP, using the ADAPT Portal and being exposed to ADAPT implementation strategies, collected using quantitative and qualitative methods. Data will be collected at T0 (baseline, after site engagement), T1 (6 months post Go-live) and T2 (12 months post Go-live).

**Discussion:**

This will be the first cluster randomised trial to establish optimal levels of implementation effort and associated costs to achieve successful uptake of a clinical pathway within cancer care.

**Trial registration:**

The study was registered prospectively with the ANZCTR on 22/3/2017. Trial ID ACTRN12617000411347

## Background

Anxiety and depression are the third largest causes of disability in Australia, impacting on family and social functioning, work performance, suicidal ideation, and survival [1, 2]. Rates of anxiety and depression are significantly higher in cancer patients than in the general population with point prevalence estimates of 20.7% for any mood disorder [3]. Despite high acceptance that psychosocial care is integral to quality cancer care, anxiety and depression are often undetected and their impact on patients under-estimated [4] in busy cancer services. Consequently a high unmet need for psychosocial care is persistent in cancer patients [5], despite the large evidence-base that interventions for anxiety and depression in patients with cancer are effective in the short and long-term [6, 7].

Because anxiety and depression are often under-detected, routine screening of all cancer patients for psychological distress using validated, reliable, objective measures, is internationally endorsed [8]. The International Psycho-Oncology Society (IPOS) and 68 affiliated organisations have set a standard of care that calls for monitoring distress as the “6th vital sign”. In Canada, cancer services have demonstrated that national screening of patients for distress is acceptable, feasible, and can be implemented [9], yet in Australia screening is not standard practice, and occurs to a variable extent across services.

Screening and detection, however, are only part of the solution. Several recent systematic reviews [10–12] highlighted the most significant predictor of improved patient outcomes as receipt of appropriate care after screening [10, 12]. Yet in the studies evaluated, only one in three patients received treatment after a positive screen for distress. In Australia, patterns of referral, treatment and follow-up of detected anxiety and depression vary across services. To address under-referral and inadequate management, a clear, empirically validated, clinical pathway to manage anxiety and depression is needed. Clinical pathways are standardised, evidence-based multidisciplinary management plans, which identify an appropriate sequence of clinical interventions, timeframes, milestones and expected outcomes for one or more patient groups. Clinical pathways have been shown to improve patient outcomes [13].

### ADAPT clinical pathway: background and development

A clinical pathway for screening, assessment and management of anxiety and depression in adult cancer patients (ADAPT CP) was developed to guide best practice in Australia [14]. The ADAPT CP is based on a review of the evidence and was refined through comprehensive stakeholder review and a Delphi consensus process [15]. Self-management and patient empowerment are built into the ADAPT CP and are important principles underlying its structure. The ADAPT CP follows a stepped care model incorporating iterative screening at recommended intervals, with triage to one of five steps (from universal care and self-management for those with minimal or mild levels of anxiety and/or depression, to specialist care for those with severe anxiety and/or depression), with review and change in step where necessary. Evidence-based recommendations on staff responsibilities, and content and timing of interventions, are provided for each step and tailored to available resources [14].

The ADAPT CP recommends formalised routine screening for anxiety and depression using the Edmonton Symptom Assessment System (ESAS-R) [16] or Distress Thermometer (DT) [17] as brief screening tools, combined with a more detailed tool, such as the Hospital Anxiety and Depression Scale (HADS) [18], to identify likely caseness (a clinical diagnosis). A structured clinical interview is required to confirm diagnosis.

While clinical pathways have shown considerable success in bringing about change in patient management, the context and implementation strategies utilised when introducing them into routine care are critical to success [19, 20]. Failed intervention implementation efforts can disrupt work flows, add significant staff burden and increase staff resistance to future interventions [21]. The Promoting Action on Research Implementation in Health Sciences (PARiHS) framework posits that successful implementation occurs when evidence is robust, the context receptive to change, and the change process appropriately facilitated with care taken to address barriers [22]. We conducted a barrier analysis [23] which, similar to studies outside the cancer setting [24, 25], identified lack of resources, education and training and support from leaders, poor uptake by patients, and lack of integration within the community, as key.

### ADAPT resources

In response to these identified barriers, our team developed and tested a number of online resources to support implementation of the ADAPT CP, including a web-based management system to operationalise the pathway tailored to site-specific staffing and resources (the ADAPT Portal), patient education materials, health professional education modules and an online cognitive-behavioural therapy program for anxiety and depression in patients with cancer (iCanADAPT) [26].

*The ADAPT Portal* prompts patients to complete validated screening and assessment questionnaires; alerts health professionals by system flags and email when a patient has elevated anxiety or depression; describes the pathway relevant to that individual patient and appropriate staff responses; provides standardised templates for referral and progress review to/from mental health services when required; and schedules ongoing follow up screening of patients at pivotal times/visits. The ADAPT Portal was pilot-tested in early 2017 (paper under review) and shown to be feasible, technically operational and acceptable.

*The ADAPT patient education materials* explain the importance of screening for anxiety and depression, the process involved for patients in the use of the ADAPT CP and Portal, and links to existing patient/caregiver resources about cancer-related anxiety and depression. A pilot study using qualitative methods with 20 current cancer patients and survivors showed the materials to be acceptable, and at an appropriate reading level (paper under review).

*The ADAPT online health professional education modules* were developed using evidence-based learning principles and spaced education to promote interactive learning. This education targets screening, assessing severity, making a referral - particularly when patients are reluctant - and empathic communication. Modules are available on eviQ Cancer Education Online (www.eviq.org.au), a widely used Oncology education site in Australia, via links in the ADAPT Portal. These education modules were pilot tested in a pre-post simulation study with 12 Oncology nurses and found to be acceptable, feasible and to associated with increased skills (paper in preparation).

*A program delivering online cognitive-behavioural therapy* for anxiety and depression has been developed for patients with early stage cancer (iCanADAPT Early). The therapy includes behavioural activation, cognitive restructuring and problem solving, and mindfulness strategies, completed in 6–8 sessions over 10–12 weeks. This online program is available in the ADAPT Portal for patient self-referral or clinician referral. Participants complete a short screening instrument (the K-10) [27] before each online lesson. A clinical psychologist monitors the progress of participants enrolled in iCanADAPT and contacts those with persistently elevated scores to assess need for referral to face-to-face therapy. iCanADAPT Early has been piloted [26] and evaluated in a randomised controlled trial and shown to be effective in reducing anxiety and depression compared to a care-as-usual control group (paper under review).

### Implementing the ADAPT clinical pathway in cancer services

There is a growing evidence-base that various strategies (such as presenting evidence that the intervention is effective; local, respected champions to promote the intervention; systems that reduce the burden of implementation as much as possible; and ongoing audit and feedback on implementation adherence and success) increase the likelihood of successful implementation [28]. However, there is little clarity regarding the optimal combination and dose effect of implementation strategies, and almost no data about the costs of implementation. Without such data it is difficult for health systems to incorporate CPs into routine delivery of care.

In this study we aim to determine the optimal “dose” of implementation effort and cost required to effectively achieve adherence to the ADAPT CP. Thus, cancer services participating in the study will be randomised to a standard (Core) implementation strategy versus a supported, tailored (Enhanced) implementation strategy for the ADAPT CP.

## Methods and design

### Primary objective

The primary objective of the ADAPT Cluster randomised controlled trial (Cluster RCT) is to evaluate the efficacy and cost-effectiveness of two implementation strategies (Core versus Enhanced) in achieving adherence to the ADAPT CP.

### Secondary objectives

Secondary objectives are to:i.describe adherence to each component of the ADAPT CP and predictors of adherenceii.describe the acceptability, adoption, appropriateness, feasibility and fidelity of individual implementation strategies and resources used to support implementation of the ADAPT CP in cancer services in NSWiii.evaluate staff and patient acceptability of the ADAPT CP, within a NSW health contextiv.describe the costs of the ADAPT CP and compare the costs of the two implementation strategies (Core vs. Enhanced) used to facilitate uptake of the ADAPT CPv.evaluate the cost effectiveness of two implementation strategies (Core vs. Enhanced) used to facilitate uptake of the ADAPT CPvi.describe levels of anxiety and depression of patients participating in the ADAPT CP over a 12-month period, and patients’ allocation to five clinical, subclinical and non-clinical categories of anxiety and depression by staffvii.describe referral patterns of cancer services before and after the introduction of the ADAPT CP, including uptake of referrals by patients.

### Hypotheses

(Note, methods used to measure each outcome referred to in the hypotheses are described in the Measures sub-section of the Methods and design section below.)

#### Primary hypothesis

Adherence to the ADAPT CP (yes/no, defined as having completed 70% or more of the recommended ADAPT CP components) will be greater in the Enhanced implementation arm than in the Core implementation arm.

#### Secondary hypotheses

Adherence to the ADAPT CP and predictors of adherenceAdherence to each component of the ADAPT CP (yes/no) will be greater in the Enhanced implementation arm than in the Core implementation arm.Adherence to the ADAPT CP will increase from the 6- to 12-month follow-up.Staff-perceived individual and site readiness to change will be associated with adherence to the ADAPT CP.Staff use of the ADAPT resources will be associated with adherence to the ADAPT CP.Characteristics of the service (size, psychosocial staffing, existing psychosocial screening), will influence staff attitudes and adherence to the ADAPT CP.Greater awareness/use and perceived utility of implementation strategies will be associated with better adherence to the ADAPT CP.Acceptability of the ADAPT CP and resources7.The ADAPT CP will be acceptable to staff and patients.8.At least 60% of staff will be aware of, use, and rate as useful, the ADAPT resources (including the health professional training and the ADAPT Portal).ADAPT implementation strategies (Core and Enhanced)9.Both Core and Enhanced ADAPT implementation strategies will be feasible (delivered) and delivered with fidelity as planned.10.At least 60% of staff will be aware of, use, and rate as useful, both Core and Enhanced ADAPT implementation strategies.11.Acceptability, adoption, appropriateness, feasibility, fidelity, and penetration of implementation strategies will be greater in the Enhanced implementation arm than the Core implementation arm.12.Improvements in staff-reported acceptability of the ADAPT CP and perceived readiness to change will be greater at 6- and 12-month follow-ups in the Enhanced implementation arm compared to the Core implementation arm.Cost-effectiveness13.While more costly, the Enhanced implementation arm will achieve greater adherence than the Core implementation arm.Patient outcomes14.Anxiety and depression screening scores at rescreening will be significantly lower than at the initial screen.

### Study design and setting

The study is a Cluster RCT being undertaken in the state of New South Wales (NSW), Australia. NSW health services are managed through 15 local health districts and three specialty networks. Twelve cancer services will be stratified by size of service - large (≥100 new pts./year) versus small (< 100 new pts./year)) to ensure equal patient volume in the two study arms. The sites will then be randomised at the cancer service level to a Core implementation strategy arm versus an Enhanced implementation strategy arm to facilitate uptake of the ADAPT CP.

After a 3-month period of site engagement, staff training and tailoring of the ADAPT CP and ADAPT Portal for each participating cancer service (site), that site will “go-live” and implement the ADAPT CP for 12 months, as part of routine care. ADAPT research staff will deliver the Enhanced or Core implementation strategies over that period, according to randomisation. The study uses a mixed methods design. Both quantitative and qualitative data eliciting staff attitudes to and experiences of the ADAPT CP and implementation strategies utilised, will be collected at T0 (baseline - after site engagement, at ADAPT go-live), T1 (6 months post go-live) and T2 (12 months post go-live).

Taking into account the governance, engagement and implementation phases, each site will participate in the study for a period of 18 months. Three sites will be activated every 3 months. Thus, all sites will have completed the study over a 30 month/2.5-year period.

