#### Inclusion criteria

Cancer services will be eligible to participate if they provide care for at least 100 patients per year in NSW Australia. Eligible cancer services may operate within the public or private healthcare system. They may be whole services or single departments within services, such as tumour streams (e.g. breast cancer or haematology) or treatment streams (such as medical or radiation oncology). If there is more than one department/hospital which shares common staff members, they will be considered one site for the purpose of this study. This is necessary to ensure that participating staff members are not exposed to both Core and Enhanced implementation strategies.

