### Statistical methods

#### Sample size and justification

##### Power for primary endpoints

Based on cancer registry data for NSW (2009) (https://www.cancerinstitute.org.au/data-research/data-held-by-cinsw/nsw-cancer-registry), approximately 37,525 patients in NSW will be diagnosed with cancer in NSW each year. Based on prior epidemiological studies, 42–45% and 35–37% of these will experience mild depression or mild anxiety, respectively [3, 36, 37] and 22–36% and 20–30% will experience moderate to severe depression and/or anxiety respectively.

Based on incidence and prevalence of cancer in NSW, a conservative estimate of 464 screening events per site (total sample of 5568 screening events in 12 sites), there is at least 80% power to detect a difference in adherence rates of 30% in the Core and 60% in the Enhanced arm using a two-tailed test with Type 1 error rate of 5%. The sample size has been adjusted for the variance inflation factor due to the clustered design and can accommodate an intraclass correlation coefficient (ICC) as high as 0.14 to achieve 80% power and 0.10 to achieve 90% power [38, 39]. Although estimates of the ICC are not available, we expect the ICC will be within this range. Based on the Cancer Institute figures, we do not envisage any difficulty in recruiting the required sample for this study. Note that the number of screening events and projected sample size and power may be revised based on screening at the first three services.

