## Discussion

This study will advance the field by identifying the level of implementation support, and resource use (Core versus Enhanced) required to effectively achieve adherence to a clinical pathway for anxiety and depression in cancer patients (ADAPT CP). It will be the first study internationally to explore this research question through a rigorous cluster randomised controlled trial, where sites are randomised to different implementation strategies. The costs and consequences of the implementation strategies will also be evaluated. The study will describe predictors of adherence, including staff and service readiness for change, staff attitudes, self-efficacy, social influence and intention to implement the CP, and staff, patient and service characteristics. A strength of the study is that adherence data, as well as potential predictors and cost data, will be collected longitudinally, allowing these factors to be explored over time.

The ADAPT CP is relevant to all cancer types and cancers of any stage. The ADAPT Cluster RCT trial will recruit cancer services providing care to a range of tumour streams, and it is intended that the ADAPT CP will be applied to all patients within these services, including those treated with curative intent and those treated palliatively. Furthermore, randomisation will be stratified by size of service to ensure inclusion of both large and small cancer services, and those within both metropolitan and rural/regional areas, to determine the implementation strategies required across a range of services likely to vary in their resources and culture. While this study is restricted to the ADAPT CP, the findings will be generalisable to other CPs, providing a broader impact on health service change.

A qualitative component is included in this study to capture the complexity of the barriers and facilitators influencing uptake of the ADAPT CP, and response to the ADAPT implementation strategies. These are expected to vary across sites with different clinical and research cultures, resources, patient populations and staffing profiles, and qualitative research has value in understanding these issues.

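### The eligibility floor and the small-site stratum both sit at 100 patients a year and are not reconciled; on either reading the cut cannot guarantee equal patient volume between arms

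*Protocol article*

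**What the plan says.** Study design and setting states that "Twelve cancer services will be stratified by size of service", with the strata and their purpose given as "large (≥100 new pts./year) versus small (< 100 new pts./year)) to ensure equal patient volume in the two study arms". The count there is of new patients.

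Inclusion criteria sets the entry floor: "Cancer services will be eligible to participate if they provide care for at least 100 patients per year in NSW Australia". The count there is of patients cared for, without the word new. On what may be a site, the same section says "They may be whole services or single departments within services".

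The Discussion restates the purpose: "randomisation will be stratified by size of service to ensure inclusion of both large and small cancer services".

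Two other sections bear on the point. The Secondary hypotheses expect service size to influence staff attitudes and adherence. Primary analyses specifies a patient-level GEE, chosen to cope with unequal site sizes. It admits covariates only if they prove to be associated with adherence or shift the intervention coefficient by more than 20%.

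**The concern.** The same number serves as the entry floor and as the boundary of the small stratum, and the protocol does not define either count well enough to tell them apart. If they are one count, the two rules exclude each other: a site small enough for the small stratum is too small to enter the trial.

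The stake is balance. With 12 clusters, chance alone can leave the arms quite different in site size. Size is the only stratification factor described, and the protocol itself expects size to relate to the primary outcome. A stratification that puts every site in one cell gives no protection. One that leaves all sites from 100 upwards in a single cell gives limited protection.

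**Working it through.** **The plan's own sample-size figure first.** Power for primary endpoints takes "a conservative estimate of 464 screening events per site (total sample of 5568 screening events in 12 sites"). Its other inputs are adherence of 30% under Core against 60% under Enhanced, a two-sided 5% test and power of 80% or more. Six sites per arm is assumed, since the split is not stated.

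- Total: 12 × 464 = 5568, as stated.
- ICC 0.14: design effect 1 + 463 × 0.14 = 65.82; effective n per arm 6 × 464 / 65.82 = 42.3; power 80.3%.
- ICC 0.10: design effect 1 + 463 × 0.10 = 47.3; effective n per arm 2784 / 47.3 = 58.9; power 91.5%.

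The stated 80% and 90% therefore reproduce. If three of the six sites in each arm contributed only 50 to 100 events and the others 464, power would be 78.3 to 79.4% at ICC 0.14 and 89.6 to 90.6% at ICC 0.10. The strata are not a power problem.

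**Can an eligible site be small?** Let R be patients cared for per year divided by new patients per year. The document does not give R, so it is an assumption. An eligible small site needs R × new ≥ 100 and new ≤ 99, so new patients must lie between 100/R and 99.

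| R | New patients per year for an eligible small site |
|---|---|
| 1 (same count) | none |
| 1.5 | 67–99 |
| 2 | 50–99 |
| 3 | 34–99 |

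The stratum is empty only at R = 1. Otherwise it can be occupied, over a band whose width the protocol does not settle.

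**Balance if all sites share one stratum.** Assumptions: 12 lognormal site volumes with mean 464, floored at 100, allocated 6:6; 20,000 simulated allocations. Only the 464 comes from the document, and it counts screening events, used here as a proxy for volume. The result is the volume of the larger arm divided by that of the smaller.

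| CV of site volume | One stratum: median / 90th percentile | Split at the median, 3:3 per stratum: median / 90th percentile |
|---|---|---|
| 0.5 | 1.21 / 1.60 | 1.14 / 1.37 |
| 0.8 | 1.34 / 2.05 | 1.23 / 1.71 |
| 1.0 | 1.42 / 2.38 | 1.30 / 1.94 |

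A cruder illustration agrees. With 12 sites log-spaced from 100 to 2000 patients and a random 6:6 split, one arm's share of the patients has a 95% range of about 25% to 75%.

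**Balance if the small stratum is occupied.** Assumptions: six small sites of 50 to 99, six lognormal large sites with the mean set so that the total is 5568, and the same CVs. The median ratio is 1.55 to 1.81 without stratification and 1.28 to 1.55 with the cut at 100. With 2, 4 or 6 small sites, the cut at 100 leaves median ratios of 1.22 to 1.56 and 90th percentiles of 1.6 to 2.9. The cut helps when it has sites on both sides, but the arms can still differ widely because nothing is balanced within the large stratum.

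**The case against.** The strongest reply is that the two sections count different things: new patients in one, patients cared for in the other. Single departments may be sites, so a unit with 150 patients in care and 70 new ones is eligible and small. The Discussion expects small services, which fits that reading. This stands. A reader might infer that the small stratum is certainly empty or nearly so, but the documents do not support that. It needs either the same-count reading or a ratio and site list that they do not give.

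A reader might also set the planned 464 events per site against a small site's 99 new patients (464 / 99 ≈ 4.7 screens each) and call it a contradiction. It is not one. The 464 is an average of screening events that no single site must reach, the pathway rescreens patients, and it is not confined to new ones.

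Third, unequal arm volume does not by itself bias the comparison, and the GEE is meant to handle unequal site sizes. That is correct, and the power check agrees. But accommodating unequal cluster sizes is not the same as adjusting for a size imbalance between arms. Size enters the model only if the data-driven covariate rule selects it.

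Finally, a median cut is awkward when three sites are activated every 3 months and reserve sites are already randomised to an arm. That is a fair constraint, and the fix has to meet it. The gain is also moderate: even a median split leaves a 90th-percentile ratio of 1.4 to 1.9.

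**Conclusion.** The point holds as a failure to reconcile two stated rules, together with a claim of balance that is too strong. On the same-count reading, the small stratum holds no eligible site and stratification has no effect, contrary to both Study design and setting and the Discussion. On the patients-in-care reading, the stratum can be occupied and stratification helps, but it cannot guarantee equal volume.

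The size is moderate. Under the assumed CVs of 0.5 to 1.0, the one-stratum arm-volume ratio is about 1.2 to 1.4 at the median and 1.6 to 2.4 at the 90th percentile, against 1.1 to 1.3 and 1.4 to 1.9 with a median split. These ratios are illustrative, because the site-size distribution is not in the documents. The stated power is essentially unaffected, and no error in the primary conclusion has been shown. The change is worth making because it is cheap and concerns a factor that the protocol expects to affect adherence, but the trial does not fail without it.

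**What to change.** 1. Define annual volume once and use that definition in both Study design and setting and Inclusion criteria.
2. Set the stratum cut well above the eligibility floor so that both strata are occupied, for example at the median annual new-patient volume of the committed sites. Fix it before the randomisation list is generated and apply it unchanged to reserve sites, so that staggered activation or a replacement does not move it.
3. Allocate equally between arms within each stratum.
4. Say that stratification is meant to improve balance in patient volume, not that it makes volume equal.
5. Put the size stratum in the primary GEE as a pre-specified covariate, outside the data-driven rule in Primary analyses.

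Cost: protocol wording and a revised randomisation list. Site volumes must be known before the list is made. The covariate uses one degree of freedom: on a cluster-level count, 12 − 2 = 10 becomes 12 − 3 = 9. If sites have already been allocated, items 1, 4 and 5 can still be done, with the stratum actually used reported as such.
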